**Main objective:**

- To study the effectiveness of the GraMI protocol on PLP in the amputee patient.

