**Specific objectives:**

- Design a mobile application to be able to carry out the intervention and determine its usability.

- Analyze the effectiveness of the GraMI protocol in the quality of life, functionality and psychological aspects of amputated patients.

- Know the experience of the person with PLP after amputation and identify the satisfaction obtained with the intervention

1. **DESIGN**:

A RCT with a mixed methodology will be carried out, with two parallel arms and blindly simple, following the recommendations of *the Consolidate Standards of Reporting Trials - CONSORT*(11), and a phenomenological study through semi-structured interviews, following the recommendations of *the Standards for Reporting Qualitative Research*(7) which will be carried out once the intervention is over. The clinical trial was registered at ClinicalTrials.gorv (registration number: NCT05083611).

1. **SETTING:**

It will be done at the community level individually. The intervention will be carried out by the participant himself / herself and will be supervised with a follow-up by the principal researcher. The semi-structured interviews will be individual and carried out in person or by video call once the intervention is over.

1. **SIMPLE SIZE**

The sample was calculated using the G * Power program, taking into account an alpha error of 0.5, a beta error of 0.8, and an effect size of 0.81(9). In order to calculate the sample we rely on existing scientific evidence. A study11 has been selected to assess phantom limb pain using the McGill Pain Short-Form Questionnaire, and the intervention used is based on mirror neurons. The total number of participants would be 50, with 25 in each group.

1. **INCLUSION AND EXCLUSION CRITERIA:**

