**Step 2: RCT**

The RCT description was performed following the *Templeate for Intervention Description and Replication (TiDier)* guide 26 in order to adequately describe all aspects of the intervention and promote study replication.

The duration of the intervention, both in the control group and in the intervention group, will be 9 weeks plus 12 weeks of follow-up. The estimated start date for recruitment will be March 2022 and will run until March-April 2023.

Both the participants in the control group and the intervention group will initially receive an educational session, in person or online, on the physiology of PLP, brain plasticity and the importance of rehabilitation. It will last approximately 30 minutes where they will be explained in detail that after an amputation there is an incongruity of visual, sensitive and motor information and maladaptive plasticity due to adjacent areas occupying the areas injured by the amputation. . This educational session will be given by the principal investigator of the project, who has clinical experience, teaching and research in the field of neurorehabilitation and pain.

Control group intervention:

After the educational session, the participant will continue with the conventional treatment he / she is receiving at that time. Participants will be provided with a follow-up diary in which they will have to record their activities, specifying the nature, frequency and duration of each activity.

At the end of the study, if the hypothesis that the GraMI protocol is effective in reducing the PLP is verified, the option will be given to the participants in the control group who can perform the intervention.

Intervention / experimental group intervention:

Participants in the intervention group will receive conventional treatment plus the GraMI protocol. If they do not receive conventional treatment, they will only perform the GraMI protocol.

GraMI protocol:

Education:

At the beginning of each of the three phases, there will be an educational session of approximately 30 minutes. During each of the sessions, online or in person, the purpose of the phase in which it is located will be explained, the procedure to be followed, common objectives will be established for each phase and the normal parameters to which must be reached in the laterality recognition phase:

- Accuracy of more than 80% of accurate images.
- Average image recognition speed.

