**- Dependent variables:**

o Phantom limb pain: Short form McGill Pain Questionnaire. It is a scale that assesses pain from a quantitative and qualitative point of view. It consists of 15 pain descriptors, of which 11 are sensitive categories and 4 are affective. In addition, it contains an analog visual pain scale. It is self-answering and each descriptor has three columns (medium, moderate, severe), where the participant must mark the degree to which that descriptor persists in their pain. If you are not present, you can leave it blank. Columns are categorized as 0; no pain, 1; mig, 2; moderate, 3; severe. It takes between 2-5 minutes to be answered.

o Quality of life: EuroQol-5D-5L(15). It is a self-challenging scale consisting of 5 dimensions: mobility, self-care, regular activities, pain / discomfort and anxiety / depression. Each dimension has 5 levels: no problems, mild, moderate, severe and extreme problems. The participant is asked to indicate his / her state of health by ticking the box together with the most appropriate statement in each of the 5 dimensions. In addition, it contains a numerical scale from 0 to 100 to quantify the degree of health on the day of the assessment. It takes between 5-7 minutes to be answered.

o Functionality: Functional Independence Scale (FIM) (16). It is a scale built on 18 items within 6 areas of operation: personal care, sphincter control, mobility, gait, communication and social knowledge. The maximum score for each item is 7 and the minimum is 1. It takes 5 minutes to be answered.

o Psychological aspects: Beck depression inventory (17). It is a self-answering scale of 21 questions. Each question is quantified on a 4-point scale ranging from 0 to 3, with 0 experiencing no symptoms and 3 experiencing symptoms severely. It takes between 5-10min to be answered.

The following is a timetable detailing when each of the variables set out above will be collected.

| **Variable** | **Scale** | **Baseline** | **Post-intervention (9weeks)** | **Follow-up**  **(12 weeks post-intervention)** |
| --- | --- | --- | --- | --- |
| Socio-demographic |  |  |  |  |
| Amputation characteristics |  |  |  |  |
| Pain | SF-MPQ |  |  |  |
| Quality of life | EuroQol-5D-5L |  |  |  |
| Funcionality | FIM |  |  |  |
| Psychological aspects | Beck |  |  |  |

1. **STATISTICAL ANALYSIS:**

When performing a randomized cynical trial with mixed methodology we find two differentiated data analyzes.

Quantitative analysis:

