The data obtained as study variables will be coded at the end of the collection, processed and analyzed by the members of the research group.

The population to be used as a sample in the analysis will include all participants who meet all the inclusion criteria, do not have any exclusion criteria and have given their consent to participate in the study. If a participant leaves before completing the study, he / she will not be replaced by another participant.

In the case of participants who have not completed the study due to dropout, have not fully completed treatment, or have even changed treatment, any data that may have been collected will be analyzed for intent to treat. The minimum number of sessions to be considered for the results will be 80%.

The program to be used for statistical analysis will be the SPSS5 program. A confidence level of 95%, and / or a statistical significance p <0.05 will be considered.

If a deviation from the intended method is considered necessary during the data analysis process, the reasons for any change will be fully documented.

To describe the sample, a descriptive statistic will be performed analyzing the mean, standard deviation, minimum, maximum and percentages of the sociodemographic variables. In addition, it will be possible to look at the average of those included and excluded in order to justify the excluded people. In this way it will be possible to describe the sample and observe the homogeneity between groups.

Next, a univariate and bivariate statistical analysis will be performed. First of all, it will be assessed whether or not the study follows a normal distribution in each of the variables. This analysis will determine whether to use parametric or non-parametric tests in the analysis of results based on the "p" value.

Equality of variance will then be analyzed through the Levenne test and finally the results will be analyzed. There will be a pre- and post-intervention analysis between groups and intragroups with a three-month follow-up. We can also analyze possible correlations between variables.

Qualitative analysis:

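### The protocol promises a yes/no verdict on whether GraMI reduces phantom limb pain, but names no deciding score, visit or contrast and sets within-group tests beside between-group tests at the same threshold

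*Protocol*

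**What the plan says.** **Objective.** The main objective is "To study the effectiveness of the GraMI protocol on PLP in the amputee patient". It names no score, time point or comparison.

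**Instrument.** Under Dependent variables, PLP is measured by the SF-MPQ: "It consists of 15 pain descriptors, of which 11 are sensitive categories and 4 are affective". The same entry adds a visual analogue pain scale (VAS). It does not say which score or scores will be analysed, and it mentions no total.

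**Visits.** Under Variables, there is a baseline assessment, one at 9 weeks and one 12 weeks after the intervention ends. Neither post-baseline visit is called primary.

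**Contrasts and threshold.** Under Statistical analysis, Quantitative analysis: "There will be a pre- and post-intervention analysis between groups and intragroups with a three-month follow-up". One general rule applies: "A confidence level of 95%, and / or a statistical significance p <0.05 will be considered".

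**Verdict.** In Step 2 (RCT), under the control group intervention, controls will be offered GraMI at the end of the study "if the hypothesis that the GraMI protocol is effective in reducing the PLP is verified". Step 1 makes the same commitment. No rule says which result decides.

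**Sample size.** "The total number of participants would be 50, with 25 in each group". The basis is described only by instrument: "A study11 has been selected to assess phantom limb pain using the McGill Pain Short-Form Questionnaire".

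**The concern.** The protocol commits to a binary conclusion and lists several analyses that could each be read as supporting it, without giving any of them precedence. Two problems follow.

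First, a pre-post test in the GraMI arm does not estimate the effect of GraMI. Entry requires a VAS of at least 3, so some regression to the mean is plausible in both arms. Both arms also receive the initial educational session, and usual treatment continues. An improvement from any of these would make the within-group test significant although GraMI adds nothing. Finding significance in one arm and not in the other does not repair this, because it is not a test of the difference between arms.

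Second, even among between-group tests, two visits and an unstated number of scores, each at 0.05, give more than one chance of a false positive.

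At stake are the trial's main claim and the offer of GraMI to controls that depends on it.

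**Working it through.** **1. The plan's own figure.** Inputs from the sample-size section: "taking into account an alpha error of 0.5, a beta error of 0.8, and an effect size of 0.81(9". Read as two-sided alpha 0.05, power 0.80 and d = 0.81, for a two-sample t-test with 25 per arm:
- noncentrality = 0.81 × √(25/2) = 2.864; df = 48; critical t = 2.011; power = 80.1%.
- With 24 per arm, power is 78.4%, so 25 per arm is the smallest size that reaches 80%.

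N = 50 is therefore reproduced as one between-group comparison at 0.05. Alpha of 0.5 as printed would need only 7 per arm for 80% power, so it is evidently a misprint. That is a separate matter.

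**2. Within-group tests when both arms improve equally.** The protocol gives no expected change in controls. I assume an equal mean improvement of δ, in SDs of the change score, in both arms, with 25 per arm and the arms independent. The probability p that one paired t-test is significant in the direction of improvement comes from the noncentral t with df = 24 and noncentrality 5δ. The chance of significance in GraMI but not in control is p(1 − p).

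| δ (assumed) | p, GraMI arm | GraMI only: p(1 − p) |
|---|---|---|
| 0.2 | 15.9% | 13.4% |
| 0.4 | 48.4% | 25.0% |
| 0.6 | 82.1% | 14.7% |
| 0.8 | 97.0% | 2.9% |

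The true difference between arms is zero in every row. p(1 − p) cannot exceed 25%, and δ = 0.4 sits almost at that maximum, so it must not be quoted alone.

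**3. Between-group tests only, no effect.** The number of tests is k = scores × 2 visits. The number of scores is an assumption: one; two (for example sensory and affective); or four (sensory, affective, total and VAS). The test statistics are simulated as equally correlated standard normals with correlation ρ, each tested at two-sided 0.05 (1,000,000 draws). The protocol gives no correlations, so ρ from 0.3 to 0.8 is assumed.

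| Scores × visits | At least one p<0.05, ρ = 0.8 to 0.3 | At least one favouring GraMI, ρ = 0.8 to 0.3 |
|---|---|---|
| 1 × 2 | 7.8% to 9.5% | 3.9% to 4.8% |
| 2 × 2 | 11.5% to 17.4% | 5.7% to 8.8% |
| 4 × 2 | 15.8% to 29.9% | 7.9% to 15.1% |

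The nominal rates for a single test are 5% and 2.5%. The right-hand column is the one that matches a claim of pain reduction.

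**4. After the fix.** One score, one visit and one between-group test at two-sided 0.05 has a 5% error rate (2.5% in favour of GraMI) and the 80.1% power of step 1. If both visits were instead to carry the claim at 0.025 each, power at 25 per arm would be 70.8%, and 31 per arm would be needed for 80%. The existing size therefore supports one primary contrast.

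**The case against.** The strongest reply is that the protocol nowhere says any significant test will do. It lists analyses and leaves the decision rule open, and multiplicity details are commonly left to the SAP, which is not shown. A partial hierarchy also exists. PLP is the sole main objective, the removal criteria treat pain as the main variable, and quality of life, functionality and psychological aspects are specific objectives. The sample size reproduces as a single two-group comparison, and the 9-week and follow-up visits carry different labels.

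Most of this is fair. A reader might infer that the verdict can be claimed from any of eight tests, with a false-positive risk of 34% (1 − 0.95⁸ = 0.337). The documents do not support that. Four separately analysed scores are not stated. Independence cannot hold, because the scores come from the same patients and a total contains its own subscores. The figure also counts results favouring control, which could not support a claim of pain reduction.

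What does not fall away is the explicit plan for intragroup tests beside between-group tests, at the same threshold and without precedence, together with a yes/no verdict. That is a choice made in the protocol, not a detail deferred. The labels on objectives and visits do not say which pain score, which visit or which contrast decides.

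**Conclusion.** The point holds as an unspecified decision rule combined with badly placed within-group testing. It does not hold as a written rule that any p-value wins.

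The within-group part weighs more. With no difference between arms, a GraMI-arm pre-post test is significant in about 16% to 97% of trials, and the pattern of GraMI significant and control not occurs in about 3% to 25%. These figures rest on an assumed equal improvement of 0.2 to 0.8 SD of change.

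For between-group tests alone the excess is modest if one score is used (about 8-10% in either direction, 4-5% favouring GraMI). It grows to 11-17% and 6-9% with two scores, and to 16-30% and 8-15% with four. The score counts and the correlations of 0.3 to 0.8 are assumptions. Every case exceeds its nominal rate, so the direction of the conclusion does not depend on them, only its size.

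**What to change.** Add a short paragraph to the quantitative analysis section:
- Name one primary contrast: the between-group difference at 9 weeks in the SF-MPQ score on which the 0.81 was based, tested at two-sided 0.05. The protocol does not say which score that was, so the sponsor must confirm it.
- State that the hypothesis counts as verified on that contrast alone, and refer to it in Steps 1 and 2.
- Label the follow-up visit and the other SF-MPQ scores secondary.
- Label within-group changes descriptive or secondary, and state that they cannot support the effectiveness claim.

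N = 50 is unchanged, with 80.1% power at d = 0.81. The cost is a paragraph of wording, and that secondary or within-group results can no longer carry the main claim.

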Day 1-5: Images in neutral positions in the different planes.

Day 6-10: Images in different positions in the different planes.

Day 11-15: Interaction with objects and functional activities.

Each activity will also be recorded through the app. Before the start of the motor imaging phase, during the educational session, the project researcher will assess the person’s ability to imagine through the kinesthetic and visual imagination questionnaire (KVIQ) 12. It is a 10-item quiz where the physiotherapist teaches different movements and the person has to rate their ability to imagine them in the first person. In the event of a impairment of imagination, the person will be taught different strategies to do so. One of them will be before the intervention to show him/her videos and images of the affected limb in order to pre-activate the areas through the observation of the action. Another strategy is to make your imagination run wild first or try to find a factor or situation that helps you to imagine it. On the other hand, pain can occur during the imagination phase. If it appears, the person can be instructed to first imagine the movement with the healthy limb. If the pain is still triggered, we can ask you to imagine the movement in the third person. These strategies will be modified throughout the intervention to allow the person to realize the mental imagination in the first person.

Phase 3. Mirror therapy:

This phase is done with a mirror box, the mobile application is no longer used. The mirror box will be provided by the research team and once the intervention is completed, it must be returned. The participant should place the mirror in the sagittal plane between the two extremities, so that he observes the healthy end in the mirror (reflection) and the amputated end is behind the mirror. The limb behind the mirror should initially have no voluntary contraction or intentional contraction. The participant will later be asked if he or she intends to contract the stump. The size of the mirror will vary depending on the level of injury and the joints involved. If pain appears during the intervention, external factors can be sought to help tolerate the intervention (music, images ...). However, if the pain persists, it should be stopped at that time.

- Session intensity: 20 minutes
- Frequency: Once a day.
- Phase duration: 5 days a week for three weeks
- Phase progression:

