The researcher conducting the interview will be an external person who has not performed the intervention or randomization, so as not to influence the questions and answers. This person has theoretical sensitivity about PLP and mirror therapy and this will make it easier to delve deeper into the topics during the interviews and better understand the experience. Subsequently, two members of the research group will perform the transcripts and analysis of the results. The aim of this triangulation is to achieve the highest possible objectivity in the results. The interviews will be recorded in voice and video format in order to be able to make a transcript as optimal as possible and will help not to lose the facial and body expressions of the participant. Only the research group and the researcher who conducted the interviews will have access to the recorded material. Each participant will have previously signed the consent to the image and voice rights. Once the study is complete, the recordings will be deleted. Once the transcripts have been completed, they will be sent to each participant to corroborate the information. This process will also be performed after the analysis of the results. You can see the consent form and the interview template in the appendices.

1. **VARIABLES:**

The assessments will be carried out by two people outside the intervention and the phenomenological study. These people will be two physiotherapists with clinical experience in the field of neurorehabilitation and / or pain, trained in research methods, calibrated with each other in order to minimize bias and will be blinded by the assignment of the groups. An initial assessment, a post-intervention assessment (9 weeks) and a follow-up assessment (12 weeks post-intervention) will be performed. The assessments will be carried out in the homes of the participants, in person and will last approximately 25-30 minutes.

The variables to be studied are differentiated between sociodemographic variables, amputation characteristics, independent variables and dependent variables. The first assessment will be the one that will last longer as all the variables will be collected, but the second and third assessment will last approximately 30 minutes as only the dependent variables will be collected.

- **Socio-demographic variables**; gender, age, marital status, height, level of education, level of physical activity, pathological and traumatic history, drugs administered and dose.

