Qualitative analysis is a non-linear, interactive and dynamic process. It will consist of different parts following Colaizzi’s 7-stage method (18). We will start by transcribing the interviews and familiarizing ourselves with the data, then coding those ideas that are related to the research question. The codes obtained will be grouped into subcategories that share common aspects and will be described and located in the phenomenon studied. Finally, these subcategories will be categorized by looking for general ideas and possible relationships. The analysis will be performed through the program Atlas.ti 8.0.

1. **ETHICAL ASPECTS**

Recommendations for Good Clinical Practice: This study is based on the recommendations of Good Clinical Practice, the Declaration of Helsinki of the World Medical Association (mentioned in the 64th General Assembly, Fortaleza, Brazil, October 2013) and the applicable legal regulations. Therefore, all the researchers involved will sign a certificate of having read and understood this statement. If necessary, an adverse event notification form will be included in the appendices. It is necessary to maintain a rigorous and continuous quality control, which can guarantee the accuracy and scientific rigor of the data obtained, maintaining the conditions of homogeneity during the process of collecting the information. If necessary, the creation of a logistics committee will allow the proper coordination of all study groups and work to contrast the scientific coordination, methodological advice and the quality of the information obtained.

Information to be provided to participants and type of consent to be requested in the study: The model information to be provided to participants and the type of informed consent to be requested will be specified in the annexes to this effect. The appendices will also include, if necessary, a waiver sheet to allow participants to leave the study at any time. All participants will be verbally informed during the process of inclusion in the study by one of the researchers and will be sent online the fact sheets with all the detailed aspects. Subsequently, they will be asked for informed consent. They will also be provided with the consent form on image and voice rights.

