Confidentiality: the strictest rules of professional conduct and confidentiality must be maintained at all times, and compliance with Regulation 2016/679 of the European Parliament and of the Council of 27 April 2016 on the protection of individuals ( RGPD) and Organic Law 3/2018, of 5 December, on the Protection of Personal Data and the Guarantee of Digital Rights (LOPD-GDD). The participant's right to confidentiality is paramount. The identity of the participant in the study documents must be coded, and only authorized persons will have access to personally identifiable details in the event that the data verification procedures require the inspection of these details. Identifiable personal details must always be kept confidential and will only be accessed by the principal investigator, the promoter and the persons authorized by the principal investigator and the relevant Health Authorities. In relation to the phenomenological study, it will not be possible to encode the identity of the participants as during the transcription phase we will have the video of the participant. The person responsible for making the transcripts will at all times guarantee the confidentiality of the data and once the transcripts have been made the videos will be deleted.

We can see all these documents in the appendices.

1. **EXPECTED BENEFITS**

At the participant level, the GraMI protocol is expected to decrease the DMF and, as a result, improve the quality of life and reduce the associated psychological factors.

At the level of participating hospitals, it is expected that they will be able to know a standardized way of applying IMG in this profile of patients.

At the level of the research group, it is expected to make communications in conferences and publications on the protocol and the results obtained, as well as its dissemination and implementation. In addition, the aim is to advance the doctoral thesis and try to get funded projects to continue research in this field.

1. **POSSIBLE UNWANTED OR SIDE EFFECTS**

The intervention is not invasive, so no serious side effects are expected with the intervention.

1. **COMPENSATION OR INSURANCE FOR PARTICIPANTS**

There is no consideration or insurance for the participants. If they wish, evolution reports can be prepared, comparing the initial, final and follow-up status of each participant.

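### The protocol foresees pain during GraMI sessions but plans no systematic recording of it, of sessions stopped because of it, or of other adverse events

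*Protocol*

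**What the plan says.** All references are to the protocol.

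- **Procedure, Step 2, Phase 2 (motor imagery):** "On the other hand, pain can occur during the imagination phase". Alternative imagery strategies follow. Recording the episode is not mentioned.
- **Procedure, Step 2, Phase 3 (mirror therapy):** "If pain appears during the intervention, external factors can be sought to help tolerate the intervention", and then "However, if the pain persists, it should be stopped at that time". Again nothing is said about recording the event.
- **Possible unwanted or side effects:** "The intervention is not invasive, so no serious side effects are expected with the intervention". The pain foreseen in Phases 2 and 3 is not mentioned here.
- **Ethical aspects:** "If necessary, an adverse event notification form will be included in the appendices".
- **Variables:** after baseline, "the second and third assessment will last approximately 30 minutes as only the dependent variables will be collected". The dependent variables are the SF-MPQ, EQ-5D-5L, FIM and Beck inventory. None is an adverse-event item.
- **Main outcome:** "Phantom limb pain: Short form McGill Pain Questionnaire". It includes a visual analogue scale and is taken at baseline, at 9 weeks and 12 weeks after the intervention ends.

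**The concern.** More pain is the most obvious harm of a pain treatment that participants carry out largely alone at home. The protocol names the event and says how to respond, but gives no place to write it down. Data that are never collected cannot be supplied later by an analysis plan, so this is not a detail that can wait for one.

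Two things are at stake. The first is the harms report: how many participants had pain provoked by a session, how often a session was stopped for it, and what else went wrong. The second is interpretation of the main result. Provoked pain could lead someone to skip sessions or to change pain medication, and a medication change is a removal criterion. If reasons are not recorded, losses driven by pain look like any other loss.

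**Working it through.** **1. How much exposure lies between assessments**

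Inputs from Procedure, Step 2: Phases 1 and 2 each have two sessions a day, 5 days a week, for 3 weeks. Phase 3 has one session a day on the same schedule.

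- Phase 1: 2 × 5 × 3 = 30
- Phase 2: 2 × 5 × 3 = 30
- Phase 3: 1 × 5 × 3 = 15
- Total: 30 + 30 + 15 = 75 sessions per participant over 9 weeks

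With 25 participants in the GraMI arm (sample size section), that is 25 × 75 = 1,875 planned sessions. Of these, 25 × 15 = 375 are mirror sessions, the only ones for which the text foresees stopping. No assessment falls between baseline and week 9.

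**2. Whether any planned source captures the events**

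| Source | What it is stated to record | Captures provoked pain or stops? |
| --- | --- | --- |
| 9-week and follow-up assessments (Variables) | SF-MPQ, EQ-5D-5L, FIM, Beck | Pain level at the visit only |
| App (Step 1) | Completion, correct answers, reaction speed | A missed activity in Phases 1 and 2, but not its cause; nothing in Phase 3 |
| Weekly calls (Step 2) | Adherence, doubts, encouragement | No harm question stated |
| Control diary (Step 2) | Activities, with frequency and duration | No |
| Interviews (Step 3) | Experience and satisfaction, about 15 GraMI participants | No counts, no controls |
| Adverse-event form (Ethical aspects) | Not described; inclusion conditional | Cannot be relied on |

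No row provides a count of provoked pain or of stopped sessions.

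**3. Link to the main result**

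- The Removal section lists changes in medication affecting pain. It also says that medication will be collected to monitor stability. Under Variables, however, drugs and doses belong to the sociodemographic items taken at the first assessment, and later assessments exclude those items. How a change and its reason would reach the data is not stated.
- The statistical analysis section sets a minimum of 80% of sessions. If that is counted over all three phases (an assumption, since the denominator is not given), 0.80 × 75 = 60, which equals Phases 1 and 2 together (30 + 30). A participant who did no mirror therapy because of pain could meet the minimum, with no record of why Phase 3 was missed.

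**The case against.** The strongest reply is that pain is the main outcome. It is measured in both arms at three times and compared between and within groups, and nothing restricts the comparison to improvement. That stands. A reader might infer that the trial could not tell whether GraMI worsens pain. The documents do not support that, because a net worsening at 9 weeks or at follow-up would show on the SF-MPQ. What the SF-MPQ cannot do is count episodes between visits, and a lower mean score at week 9 is compatible with frequent provoked pain along the way.

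Other points also limit the concern:

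- The text says that pain can occur, not that it is expected, and it gives a stopping instruction for mirror therapy only.
- The side-effects section speaks of serious effects. It is incomplete beside Phases 2 and 3, but does not contradict them.
- The appendices are not shown. The ethics section uses the same conditional phrase for the waiver sheet, which the Participants section treats as existing. The wording therefore does not prove that the adverse-event form is absent. The point rests on the conditional wording and the variable list.
- No objective or hypothesis claims safety, so it cannot be said that the trial sets out to declare GraMI safe.
- One might size the gap by the upper 95% limit after zero events in 25 participants: 1 − 0.05^(1/25) = 11.3% one-sided, or 1 − 0.025^(1/25) = 13.7% two-sided. That limit reflects the size of the arm and would be the same with perfect recording, so it does not measure this defect.
- Telephone questions in one arm and a diary in the other would ascertain harms unequally and could make GraMI look worse. The remedy has to avoid this.

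**Conclusion.** The point holds in a limited form. Followed as written, the visible protocol leaves session-provoked pain, pain-related stops and other adverse events without systematic recording over 75 planned home sessions per GraMI participant, including 15 mirror sessions for which the app keeps no record. The trial could not reliably report these harms, nor say whether they lie behind non-completion or removal for a medication change. Its ability to estimate the net change in phantom limb pain at the two post-baseline assessments among those assessed is not in question.

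The frequency of provoked pain is not given in the document, so the number of events that would go uncounted cannot be estimated. The conclusion assumes that no appendix contains a harms form with a fixed schedule. If one does, the main text should say so and list it among the variables. The change is worth making because unrecorded episodes cannot be reliably recovered afterwards.

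**What to change.** 1. Add harms to the list of collected variables and make the adverse-event form unconditional.
2. In both arms, ask the same neutral questions in the same way at the existing 9-week and follow-up assessments: pain flare, unplanned care and change in medication since the last visit. Word them without reference to the intervention, so that they do not invite disclosure of allocation to the blinded assessors. Report counts by arm.
3. In the GraMI arm, also record at each planned weekly call any session shortened or stopped because of pain. Report this descriptively for GraMI only, since controls have no counterpart.
4. Record the reason for each removal or dropout.
5. In the side-effects section, mention the pain already foreseen in Phases 2 and 3.

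The cost is a few minutes per contact, with no extra visits. There are two limitations. The between-arm questions rely on recall over 9 and 12 weeks, and the GraMI-only data come through the unblinded principal investigator. The changes concern recording and reporting only; no clinical rule is proposed.
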